### Outcomes

The primary results will be oriented to evaluate feasibility in the implementation of the counseling intervention concerning the proposed times for intervention and the difficulties that may arise in the application of these, and the recruitment and dropout rates.

Secondary outcomes will be the exclusive breastfeeding rate in the first 6 months postpartum. We use the WHO definition of exclusive breastfeeding: “exclusive breastfeeding for at least 6 months in all infants,” meaning that the infant receives only breast milk and no other liquids or solids, not even water, except for oral rehydration solution or drops/syrups of vitamins, minerals, or medicines [19].

The previous outcome will be evaluated by home visits at 2, 4, and 6 months postnatal, and a checklist will be used to verify the adherence and maintenance of mothers to breastfeeding by asking the following: offer exclusive breastfeeding, offer food or fluids other than breast milk, ensure breastfeeding even when separated from your child (expressing breast milk), describe correct breastfeeding technique, and recognize the importance of breastfeeding for the growth and development of the newborn. Additionally, mothers will be invited to continue breastfeeding and participating in the study.

Another secondary outcome will be the level of knowledge about the breastfeeding process using a questionnaire (Table 2), based on the nursing Knowledge outcome: Breastfeeding (1800) defined as the “Extent of understanding conveyed about lactation and nourishment of an infant through breastfeeding” [18]. For questionnaire design, we select 7 indicators and construct a statement with multiple-choice answers for each one. For the evaluation, a Likert-type scale will be used with a score of 1 to 5 (1, no knowledge; 2, little knowledge; 3, moderate knowledge; 4, substantial knowledge; and 5, extensive knowledge). The internal consistency of the questionnaire was 0.8712 Cronbach’s alpha coefficient.

**Table 2 Tab2:** Items and indicators to quantify the nursing knowledge outcome: breastfeeding (1800)

Indicator 180003: composition of breast milk, milk outlet process, and initial vs late milk	
1. Occurs between 5 and 10 days after delivery	
2. Contains less sugar, fats, and vitamins of B complex and vitamin C	
3. Contains proteins, sugar, fats, minerals such as sodium, calcium, iron, selenium, zinc, and B complex vitamins and vitamins such as C, A, E, K.	
4. Its composition contains between 88% and 90% water	
5. Occurs in the first 3 to 4 days after delivery	
6. It is yellow, thick and of little amount	
7. Contains more sugar, fats, calories, and B Complex vitamins and vitamin C	
8. It occurs progressively up to about 100 ml a day	
9. Contains fewer proteins, antibodies, and vitamins A, E, K	
10. It occurs in an amount of 400 to 600 ml per day	
11. Occurs from the tenth day after delivery	
12. Contains more protein, minerals such as sodium, iron, selenium, zinc, and vitamins such as A, E, K	
13. Its composition contains 87% water	
14. It is produced in an amount of 700 to 800 ml per day	
Indicator 180001: benefits of breastfeeding	
15. Prevents breast, uterine, and ovarian cancer	
16. Prevents respiratory diseases such as bronchitis, pneumonia, and gastrointestinal diseases such as diarrhea and dehydration	
17. Prevents the onset of diseases such as allergies, obesity, high blood sugar, high blood pressure, and cancer	
18. Prevents postpartum depression states (mood affecting women after giving birth, characterized by feelings of extreme sadness and anxiety)	
19. Prevents constipation and cramping	
20. Prevents child malnutrition	
21. Facilitates the affective bond between mother and child	
22. Strengthens self-appreciation, self-confidence, and emotional satisfaction	
23. Contributes to postpartum weight loss	
24. Lowers the risk of osteoporosis (a disease that thins and weakens bones, causing them to break easily)	
25. Promotes better growth and development of physical, language, and social capacities	
26. Reduces risk of postpartum hemorrhaging or bleeding	
27. Lowers the risk of heart disease	
28. Improves intelligence	
29. Delays the return of ovulation and menstruation	
Indicator 180005: proper technique for breastfeeding the baby	
30. The mother should select the most comfortable position	
31. The baby's body must be attached to the mother's body	
32. The baby's head and body are in the same direction	
33. The mother should grab the breast with her C-shaped hand (placing her thumb above the breast and the other four fingers below the nipple and behind the areola (ring of pigmented skin around the breast)	
34. The mother should bring the child closer to the breast and not the breast to the child	
35. The mother should stimulate the baby to have a search reflex, bringing the nipple closer to the baby's lip and when it opens its mouth to insert the nipple and the areola	
36. The baby's lips should remain outside like the mouth of a fish	
37. The baby's mouth should coat the entire areola (dark area of the breast)	
38. The baby's chin must touch or almost be touching the mother's chest	
Indicator 180006: adequate position of the infant during breastfeeding	
39. Stretched or cradle position (classic or traditional)	
40. Cross-cradle position	
41. Parallel stretched position (side lying down)	
42. Rugby ball or football position (inverted)	
43. Sitting or horse position	
44. Face-up position	
45. Vertical or standing position	
Indicator 180014: signs of mastitis, duct obstruction, and nipple trauma	
46. Breast skin is shiny, red, tense, and warm	
47. Formation of a mass or lump in the breast that is palpable and painful, often with redness of the skin in that area	
48. Painful cracks or wounds on the nipple	
49. Uncontrolled fever, chills, general discomfort, nausea, vomiting, headache	
50. Formation of a mass or lump in the breast, severe pain, swollen and hardened sinus, obstruction at the milk outlet (milk does not flow), pus secretion	
51. Inflammation or swelling in the breast with a feeling of warmth	
52. Nipple pain	
53. Cracks or nipple wounds that may bleed	
54. Decreased milk flow	
55. No fever or symptoms of general discomfort	
Indicator 180015: appropriate techniques for the extraction and storage of breast milk	
56. Massage into the breast before breast milk extraction	
57. At room temperature: breast milk is preserved for up to 4 h, it is advisable to leave it in a dry place, protected from sunlight and heat.	
58. In the freezer: breast milk is kept frozen for up to 15 days, so it is recommended not to constantly open and close the freezer. If the refrigerator is two doors, breast milk can be stored for up to 3 months.	
59. With your hand in the shape of a C, place it on the breast (placing your thumb above the breast and the other four fingers below the nipple and behind the areola (dark area of the breast)	
60. In a refrigerator or refrigerator: breast milk is stored for up to 12 h, it is advisable not to place it in the refrigerator door to avoid temperature changes every time the door is opened or closed.	
61. Lean the body forward, squeeze the breast without swiping your fingers, and gently push against the ribs	
62. Then move your fingers forward and repeat the procedure as many times as necessary simultaneously and smoothly	
Indicator 180020: need for fluid intake by the mother	
63. It is advisable to increase the consumption of liquids, preferably water, as it is the largest component of breast milk	
64. Water intake during lactation should be sufficient to compensate for the loss of water through milk	
65. Vitamin C-rich juices are recommended	
66. The most recommended liquids for women during breastfeeding are water, fruit juices, and milk	
67. Avoid drinking alcoholic beverages, excessive coffee, and tea (more than 2 cups a day, during the term of breastfeeding)	

At the end of the intervention, the level of knowledge acquired will be verified and a home visit will be made at 2, 4, and 6 months after the birth of the babies. The questionnaire will be used again in each of the visits to evaluate the level of knowledge over time and a checklist will be used to verify the adherence and maintenance of mothers to breastfeeding.

### Sample size for secondary outcomes

We used STATA-12 to calculate the sample size with the following statistical parameters: a rate of exclusive breastfeeding of 70% in the experimental group and 40% in the control group, a power of 80%, an alpha error of 5%, and the rate of abandonment of exclusive breastfeeding being 2.5 times higher in the control group compared to the experimental group. Additionally, for the knowledge level outcome, we considered a delta or expected difference of 0.4 in the knowledge assessment outcome score between both groups, a power of 95%, an alpha of 5%, a standard deviation of the outcome scores of 0.5, an average of correlations between the first and second assessment of 0.5. Finally, the sample size estimated was *n* = 118 primigravidae mothers including 20% of the possible losses; distributed by simple randomization with a ratio of experimental group/control group 1:1 (*n* = 59 pregnant women in the experimental group and *n* = 59 pregnant women control group).

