### Settings and locations

The study will be carried out in two public hospitals in the cities of Girón and Piedecuesta in Santander, Colombia, which mainly provide care for low-income people. The recruitment of participants began in 2019 and is expected to end in 2021 due to delays caused by quarantines and restrictions to control the COVID-19 pandemic. The protocol is approved by the research ethics board of the Industrial University of Santander and is covered by the inter-institutional agreement between the participating hospitals; it has obtained approval and funding from the university’s Research and Extension Directorate (#2453) and additional funding from young research program form the Ministry of Science, Technology, and Innovation (#8009).

Pregnant women attending prenatal controls will be invited to participate in the study. Pregnant women who meet the inclusion criteria and sign informed consent will fill out a questionnaire designed based on the Knowledge outcome: Breastfeeding (1800). Adolescents who obtain a score on the knowledge test less than or equal to 3.8 points will be invited to participate in the intervention. Pregnant women scoring less than or equal to 3.8 in breastfeeding knowledge will be invited to participate as they are susceptible to increase breastfeeding knowledge.

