### Randomization and blinding

We will use simple randomization with an allocation ratio of 1:1. The generation of the allocation sequence will be carried out using a succession of true random numbers stored in tables of random digits. A person who does not know the participants will access this table to find out which group each participant belongs to, depending on whether the number was odd or even, and will inform the nurses who will carry out the intervention. The nurse who will perform the intervention “Lactation Counselling” will only maintain contact with the experimental group, and the nurse who will carry out the initial and final measurements along with the person who will perform the data analysis will be blinded to the group assignment. The nurses conducting the interview and statistical analysis of data will be masked in group assignments. To avoid contamination of the participants between the control group and the intervention group, they will meet on different days and times to attend the activities of the interventions.

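### Simple odd/even randomisation makes 59 per arm an expected size, and neither the allocation nor the stated analyses use hospital; adjusting for it and stratifying the remaining allocations is a cheap improvement

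*Protocol article*

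**What the plan says.** In the protocol article, Sample size for secondary outcomes gives a total of "118 primigravidae mothers including 20% of the possible losses", who are "distributed by simple randomization with a ratio of experimental group/control group 1:1". It then prints the arm sizes as "59 pregnant women in the experimental group" and "59 pregnant women control group". The Design section repeats 59 for each arm.

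Randomization and blinding states the same method, "We will use simple randomization with an allocation ratio of 1:1", and says how it works: a person who does not know the participants consults a table of random digits, and the arm follows "depending on whether the number was odd or even". No blocking, stratification or rule that closes an arm at 59 is described.

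Settings and locations states: "The study will be carried out in two public hospitals in the cities of Girón and Piedecuesta". The number of mothers expected from each hospital is not given.

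Statistical analysis lists chi-square or Fisher tests, t or Mann-Whitney tests, a repeated measures ANOVA for knowledge and a binomial regression for abandonment of exclusive breastfeeding. All are described as comparisons by treatment group. Hospital is not mentioned.

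**The concern.** Two features of the allocation deserve attention.

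First, an odd/even digit gives each mother an independent probability of one half. The arm sizes are then binomial, and the printed 59 and 59 are their mean and not something the procedure delivers. If site staff took the printed figures as totals to be met, the last allocations would no longer follow the sequence and could be foreseen.

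Second, the trial runs in two hospitals in two cities. Breastfeeding practice and usual prenatal education may or may not differ between them. Simple randomisation leaves the hospital mix of each arm to chance, and the stated analyses do nothing to take it out again. In a pilot of 118 mothers, a visible imbalance is quite likely, and the preliminary effect estimates would carry whatever hospital difference exists.

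**Working it through.** **Inputs from the article.** Total 118, 59 per arm; exclusive breastfeeding 70% against 40%; power 80%; alpha 5%; losses 20%; allocation probability 1/2 per mother (odd or even digit); two hospitals. **Assumptions.** Two-sided alpha, which the article does not state but which reproduces its figure; and the hospital split, which is not given and is shown as a range.

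**1. The plan's own figure.** Without continuity correction:

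n = [1.96·√(2·0.55·0.45) + 0.842·√(0.7·0.3 + 0.4·0.6)]² / 0.30² = 41.97.

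With continuity correction: n = (41.97/4)·[1 + √(1 + 4/(41.97·0.30))]² = 48.4, so 49 per arm. Adding 20%: 49 × 1.2 = 58.8, so 59 per arm and 118 in total. The printed total reproduces and is not in question here.

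**2. Arm sizes under the stated mechanism.** The size of one arm is X ~ Binomial(118, 1/2).

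- SD = √118 / 2 = 5.43
- P(X = 59) = C(118, 59) / 2¹¹⁸ = 0.073
- 2.5% and 97.5% quantiles: 48 and 70
- P(arms differ by 10 or more) = P(|X − 59| ≥ 5) = 0.41
- P(arms differ by 20 or more) = P(|X − 59| ≥ 10) = 0.080

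**3. What unequal arms cost.** Power for 70% against 40% after 20% loss, by the uncorrected normal approximation:

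| Split of 118 | Power |
|---|---|
| 59 / 59 | 84.5% |
| 48 / 70 (either way round) | 83.2% to 83.4% |
| Average over the binomial | 84.2% |

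At the edge of the 95% range the loss is about 1 point.

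**4. Hospital balance.** Let one hospital supply m of the 118 mothers. Of these, x go to the experimental arm, as do y of the other 118 − m, with x and y binomial with probability 1/2. The imbalance is d = x/(x + y) − (m − x)/(118 − x − y). As a quick check, with equal hospitals SD(d) ≈ √(0.25 × 2/59) = 0.092.

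| m (assumed) | P(imbalance ≥ 10 points) | P(imbalance ≥ 15 points) |
|---|---|---|
| 24 | 19% | 4% |
| 35 | 24% | 8% |
| 47 | 27% | 10% |
| 59 | 31% | 12% |

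**5. What an imbalance could do to an outcome.** The article gives no between-hospital difference. As an illustration only, suppose exclusive breastfeeding differs by 20 points between the hospitals. A 10-point imbalance then moves the arm difference by 0.10 × 20 = 2 points. The planned effect is 70 − 40 = 30 points, and its standard error at 49 per arm is √[(0.21 + 0.24)/49] = 9.6 points.

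**6. What restriction would give.** With blocks of four stratified by hospital (block size assumed, used from the start), the arms differ by at most 2 within a hospital and at most 4 overall, so each arm holds 57 to 61.

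**The case against.** The case against treating this as a fault is strong.

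- The printed 59 and 59 stand in a sample size section beside a 1:1 ratio, and the ordinary reading is planned sizes. A reader might infer that the sequence will be overridden to reach those totals. No section plans this, so it is only a risk to avoid.
- Simple randomisation is valid, unbiased and the least predictable method. The ordinary standard error already allows for chance imbalance, and the loss of power from unequal arms is trivial.
- A reader might also infer that each hospital has its own classes and nurses. The article does not say so; it names two public hospitals that mainly serve low-income people.
- The choice of covariates is commonly left to an analysis plan, and none is shown here. Silence about hospital is therefore not an omission in itself.
- The breastfeeding and knowledge outcomes are secondary and preliminary; feasibility is primary. The illustrative 2-point shift is small beside a standard error of 9.6 points.
- Recruitment began in 2019 and was expected to end in 2021, so a change of method would leave two allocation schemes in one small pilot.

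All of this limits the size of the point. What stands is that the stated mechanism does not fix the arm sizes, and that neither the allocation nor the analyses as described use hospital, although doing so would cost little.

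**Conclusion.** The point holds as a cheap improvement and not as an error in the design. The arm-size part is a matter of wording: 59 per arm is an expectation, reached exactly in 7.3% of trials, and departures from it cost about 1 point of power even at 48 and 70.

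The hospital part is the more useful one. The hospital share can differ between arms by 10 points or more in roughly 19% to 31% of trials, assuming that one hospital supplies between 24 and 59 of the 118 mothers. Whether that matters for breastfeeding or knowledge depends on between-hospital differences that the article does not give. A conclusion that the comparison is biased, or that the sample size is wrong on this account, would go beyond the document.

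**What to change.** 1. **Wording.** In Design and in Sample size for secondary outcomes, call 59 per arm the expected size. State that the sequence is followed to the end and that the totals are not forced to 59 and 59.
2. **Analysis.** Add hospital as a covariate to the knowledge model (the repeated measures analysis; the t test can stay as the unadjusted comparison) and to the binomial regression for abandonment of exclusive breastfeeding.
3. **Allocation of mothers not yet allocated.** Have the person who holds the sequence use permuted blocks of concealed, randomly varying size, with a separate list for each hospital. Mothers already allocated keep their assignment. If recruitment is complete, only items 1 and 2 apply.

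**Cost.** One extra model term and two prepared lists. Blocks add slight predictability at their ends, because the arms meet on different days and past assignments can be seen on site; varying the block size and keeping it concealed limits this. A change partway leaves two allocation schemes, and the report must say when the change was made and how many mothers were allocated under each.

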### Randomization and blinding

We will use simple randomization with an allocation ratio of 1:1. The generation of the allocation sequence will be carried out using a succession of true random numbers stored in tables of random digits. A person who does not know the participants will access this table to find out which group each participant belongs to, depending on whether the number was odd or even, and will inform the nurses who will carry out the intervention. The nurse who will perform the intervention “Lactation Counselling” will only maintain contact with the experimental group, and the nurse who will carry out the initial and final measurements along with the person who will perform the data analysis will be blinded to the group assignment. The nurses conducting the interview and statistical analysis of data will be masked in group assignments. To avoid contamination of the participants between the control group and the intervention group, they will meet on different days and times to attend the activities of the interventions.

### Ethical consideration

This research is based on the World Medical Association Declaration of Helsinki and the research guidelines in Colombia (Resolution 008430/1993 and Law 911/2004) and has the approval of the Ethics Committee in Scientific Research of the Industrial University of Santander. The parents of the participants must sign the informed consent, as well as a consent for those under 18 years of age because they are considered a population of minors.

### Statistical analysis

The information will be recorded in EpiData 3.1. An intention-to-treat analysis will be performed. We will use descriptive statistics: continuous variables will be presented using median and standard deviation after evaluation of the normal distribution of the variable, otherwise, median and minimum, and maximum values will be used. The categorical variables will be presented in absolute frequencies and relative in percentages asymmetrical. Categorical data will be summarized as counts and percentages. The categorical and continuous variables will be compared according to the treatment group using chi-square tests or Fisher’s exact tests and Student's *t* test or Mann-Whitney's *U* test, respectively. The exclusive breastfeeding rate will be calculated at 2, 4, and 6 months of follow-up with their respective confidence intervals. To evaluate the preliminary effect of the intervention on the level of Knowledge: Breastfeeding, two approximations will be made by different statistical methods: mean differences through independent samples Student's *t* test and repeated measures ANOVA with their respective confidence intervals. Additionally, the effect of the intervention on the abandonment of exclusive breastfeeding will be calculated in terms of relative risk using binomial regression.

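### The t test planned for breastfeeding knowledge makes no efficient use of the baseline score that every mother has, so its confidence interval is wider than it needs to be

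*Protocol article*

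**What the plan says.** The Statistical analysis section of the protocol article opens its commitments with "An intention-to-treat analysis will be performed". For knowledge it then announces that "two approximations will be made by different statistical methods: mean differences through independent samples Student's" test for two independent groups. The second method in that sentence is given as "repeated measures ANOVA with their respective confidence intervals". Neither method is described as adjusted for baseline, and neither is named as the main one.

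The score is available throughout. The Abstract lists baseline, post-intervention, and 2, 4 and 6 months after childbirth. Under Settings and locations, the same questionnaire is the eligibility screen, so no mother is randomised without a baseline value. The Outcomes section repeats it after the intervention and at each home visit.

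Sample size for secondary outcomes gives the planning values for knowledge. The target is "a delta or expected difference of 0.4 in the knowledge assessment outcome score between both groups", with 95% power and 5% alpha. The spread is set by "a standard deviation of the outcome scores of 0.5". The link between baseline and follow-up enters as "an average of correlations between the first and second assessment of 0.5". The section also allows for 20% losses.

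**The concern.** The plan assumes that baseline knowledge predicts later knowledge, then names a main comparison that gains nothing from that prediction. The 1:1 allocation is by simple randomisation, so the arms can differ at baseline by chance. An unadjusted t test leaves that difference in the estimate as noise.

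This matters because the Purpose section asks the pilot to estimate potential effectiveness. For knowledge, the product of the study is the estimated difference and its interval, so an interval that could be narrower at no cost is a defect even when power is ample.

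A second, smaller issue concerns the repeated-measures ANOVA. In its classical form it needs a score at every occasion. With 20% losses allowed for, that form would leave out randomised mothers who have some observed scores, which fits poorly with an intention-to-treat analysis.

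**Working it through.** **Inputs** (Sample size for secondary outcomes): difference 0.4; SD σ = 0.5; correlation r = 0.5; power 95%; alpha 5%; 59 per arm including 20% losses. Two-sided testing is assumed, since the article does not state it.

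**The plan's own figure.** The total of 118 comes from the breastfeeding outcome, "a rate of exclusive breastfeeding of 70% in the experimental group and 40% in the control group", at 80% power. The usual two-proportion formula gives 42 per arm, or 49 with continuity correction. Then 49 × 1.2 = 58.8, rounded up to 59 per arm, or 118. Knowledge does not drive the sample size:

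n per arm = 2(1.96 + 1.645)² × 0.5² / 0.4² = 40.6, so 41.

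**Variance of the group difference relative to a follow-up-score t test**

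- Follow-up score: 1
- Change score: 2(1 − r)
- Baseline-adjusted (ANCOVA): 1 − r²

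| r | Follow-up | Change | Adjusted | Evaluable n per arm, adjusted |
|---|---|---|---|---|
| 0.3 | 1.00 | 1.40 | 0.91 | 37 |
| 0.5 (plan) | 1.00 | 1.00 | 0.75 | 31 |
| 0.7 | 1.00 | 0.60 | 0.51 | 21 |

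At the plan's r, reading the t test as a test of change scores does not help: 2(1 − 0.5) = 1. Adjustment does: 1 − 0.25 = 0.75. A simulation of 4000 trials with 47 per arm gave a ratio of 0.748.

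**Size at the expected number analysed.** 59 × 0.8 = 47.2, so 47 per arm.

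- t test: SE = 0.5 × √(2/47) = 0.103; half-width 1.96 × 0.103 = 0.202; power 97.2%.
- Adjusted: SE = 0.103 × √0.75 = 0.089; half-width 0.175; power 99.4%.

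The standard error of the t test is thus about 15% larger than necessary (1/√0.75 = 1.155). Equivalently, it would take one third more mothers (1/0.75 = 1.33) for the t test to match the adjusted interval. If 49 per arm remain, as the 1.2 multiplier implies, the half-widths are 0.198 and 0.171.

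**Sensitivity to r.** At 47 per arm the adjusted half-width is 0.202 × √0.91 = 0.193 at r = 0.3, and 0.202 × √0.51 = 0.144 at r = 0.7. The lower end deserves attention: eligibility is capped at a knowledge score of about 3.8, and restricting the baseline range tends to weaken its correlation with later scores.

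**The case against.** The strongest reply is that the t test is valid and good enough. Randomisation makes it unbiased. With 47 per arm it has 97.2% power against a 95% target. Knowledge is a secondary outcome of a pilot whose primary aim is feasibility, and the gain shrinks to 9% of the variance if r is 0.3. All of this is correct, and it limits the consequence. It does not remove the point, because the aim for knowledge is an estimate with an interval, and the interval can be narrowed with data already collected.

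The 25% figure belongs to the t test only. The repeated-measures ANOVA may take baseline as one of its occasions, so the plan as a whole does not necessarily ignore baseline.

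A reader might also infer more than the article supports:

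- That incomplete mothers are dropped and the intention-to-treat statement is therefore contradicted. The article names the ANOVA and says nothing about missing scores. Deletion depends on how the model is fitted, and a rule may stand in a fuller document that is not shown.
- That a known minimum number of mothers would be lost. The 20% is an allowance for possible losses, not a floor.
- That the ANOVA would report a diluted effect. This needs baseline to be an occasion and the group main effect to be the quantity read. The article states neither.
- That repeated t tests would inflate the false-positive rate. The article does not say that the t test will be run at every visit.

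Finally, a mixed model also leaves out mothers with no follow-up score, so the proposed change reduces the missing-data problem without abolishing it.

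**Conclusion.** The point holds as a loss of precision. Under the protocol's own SD of 0.5 and correlation of 0.5, adjusting for baseline cuts the variance of the knowledge comparison by 25%. It narrows the 95% half-width from about 0.202 to 0.175 points with 47 per arm. Over correlations of 0.3 to 0.7 the variance reduction runs from 9% to 49%. The result rests on a roughly linear relation between baseline and follow-up, equal SDs in the two arms, and about 20% loss. No bias and no shortfall in planned power follow from the t test.

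On the repeated-measures ANOVA the finding is conditional: a complete-case version would be in tension with intention-to-treat unless missing scores are handled. The article does not commit to that version, so this is a risk to close and not an established contradiction.

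**What to change.** Replace the t test and the repeated-measures ANOVA as the main knowledge analysis with one baseline-adjusted model. The fuller option is a linear mixed model on the post-intervention, 2-, 4- and 6-month scores, with baseline knowledge as covariate and arm, visit and arm-by-visit as terms. It should use all available follow-up scores of randomised mothers and state the missing-data assumption (missing at random). The simpler option is ANCOVA at the post-intervention visit.

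In either case, name the adjusted difference at the post-intervention visit, with its 95% confidence interval, as the main contrast. Keep the t test as a descriptive check, and report how many mothers in each arm have no follow-up score.

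The cost is a change of wording in the Statistical analysis section. No new measurements, visits or participants are needed, and the sample size of 118 is unaffected because the breastfeeding outcome determines it.
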